#### Primary outcomes

There will be two primary outcome measures: individual fruit (excluding juices) and vegetable (including potatoes and legumes) consumption (measured as serves consumed/day). Changes in consumption of F&V servings/day, will be calculated as the mean difference, between baseline (pre-) and post-intervention (with 95% Confidence Intervals [CI]). A standard serve of fruit is approximately 150 g (approx. 5.3 oz) and a standard serve of vegetables is approximately 75 g (approx. 2.6 oz) [53].

The first two questions, that relate to children’s F&V consumption, have been chosen from the food frequency questionnaire (FFQ) used in the *Many Rivers Diabetes Prevention Project* [54]. This FFQ has been used among Australian children aged 10–12 years, and has been assessed for and found to have, criterion/concurrent/predictive validity and reliability [55].

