### Sample size

Sample size requirements estimated that 20 schools (10 per intervention arm) will be required to take part in this study, with an average of 50 students (SD ± 22, and therefore CV = 0.436) per arm. These numbers are feasible given that more than 30 schools have enrolled to participate in the program with OzHarvest, for 2021, and recruitment continues. A within-school intraclass correlation of 0.04 is estimated for both primary outcomes of fruit and vegetable intakes [71–73] and correlations of 0.5 are assumed between outcome measures between baseline and 10 weeks [56]. Standard deviations for vegetable and fruit serves/day are estimated to be 1.3 and 1.1 respectively, according to the South Australian Health Reports from 2015 on children’s vegetable intake [74] and fruit intake [75]. Allowance will be made for 20% loss due to follow-up or missing data [72, 76].

Given there are two primary outcomes (fruit serves/day and vegetable serves/day), a Bonferroni-corrected alpha (α) of 0.025 (i.e. 0.05/2) will be used. An increase of 0.5 servings of fruit/day (i.e. 75 g) and vegetables/day (i.e. 37.5 g) may be considered meaningful [56, 77], given that even small increases (e.g. 50 g/day) in combined F&V intakes have the potential to provide protection against the development of certain NCDs [77]. Under the above assumptions, the study would provide 90% power to detect an intervention effect of this size, for the vegetable intake primary outcome and 97% power for the fruit intake primary outcome.

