### Statistical analysis

Demographic and baseline characteristics will be summarised for both intervention and wait-list control groups and compared for differences at baseline. Standard summary statistics (mean and standard deviation [SD]) or non-parametric statistics (medians and inter-quartile ranges) where applicable, will be used. For the categorical variables, frequencies and percentages will be calculated and reported.

Effects of the intervention on study outcomes will be estimated with generalized linear mixed models (GLMMs) including random intercepts to account for clustering within schools and fixed effects of intervention arm, using appropriate family and link functions according to outcome distribution or type. Models will be adjusted for potential confounders: gender, grade, ICSEA, type of teacher training (face-to-face vs online vs no training), and whether the student speaks another language at home (which will be dichotomized as Yes/No). Analyses will also adjust for baseline levels of the desired outcome. Intracluster correlation coefficients (ICC) for within-school clustering in each intervention effect model will be calculated and reported. Similarly, within-group changes in outcomes will be estimated using GLMMs including random effects for schools and individuals, and fixed effects of time. Estimated intervention effects and within-group changes will be reported as unstandardized regression coefficients or exponentiated coefficients (e.g. odds ratios), with 95% confidence intervals and *p*-values.

All analyses will follow the intention-to-treat (ITT) principles and missing data will be handled using multiple imputation by chained equations [80]. Imputation of outcome variables (and covariates if missing) will be conducted separately by intervention group and will include schools and covariates as auxiliary variables [80].

To assess sensitivity of the findings to different assumptions around the missing data mechanism, complete case analyses (valid under a missing completely at random assumption) will also be conducted as a sensitivity analysis. No interim analyses of trial outcomes are planned nor any stopping rules.

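### The within-group change model lets schools differ in level but not in change, so its confidence intervals are too narrow and its p-values too small whenever schools change by different amounts

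*Protocol article*

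**What the plan says.** The Statistical analysis section of the protocol article describes two models.

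- **Intervention effect.** This is a generalized linear mixed model "including random intercepts to account for clustering within schools and fixed effects of intervention arm", adjusted for the baseline value of the outcome.
- **Within-group change.** Here, "within-group changes in outcomes will be estimated using GLMMs including random effects for schools and individuals, and fixed effects of time". The sentence is introduced as parallel to the intervention-effect model, and time appears only among the fixed effects.

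Both results carry formal inference: "Estimated intervention effects and within-group changes will be reported as unstandardized regression coefficients or exponentiated coefficients (e.g. odds ratios), with 95% confidence intervals" and p-values. Under Primary outcomes, the change in fruit and vegetable serves per day "will be calculated as the mean difference, between baseline (pre-) and post-intervention (with 95% Confidence Intervals [CI"]). The Secondary outcomes section likewise defines all its outcomes as pre-post differences.

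The Sample size section says that "20 schools (10 per intervention arm) will be required to take part in this study". It also says: "A within-school intraclass correlation of 0.04 is estimated for both primary outcomes of fruit and vegetable intakes". It adds a correlation of 0.5 between baseline and 10 weeks, but does not say how far school means correlate over the same interval.

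**The concern.** The model looks as though it handles clustering because school is a random effect. A school intercept, however, absorbs only differences between schools that are the same at both time points. It does nothing for differences in how much schools change, and those are what make a pre-post mean uncertain when an arm has only 10 schools.

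The article gives good reason to expect such differences. Under Intervention, teachers may have six hours of face-to-face training or a three-hour online version, and funding differs between schools. Under Implementation, the numbers of lessons and cooking sessions are recorded because they may vary.

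At stake are the intervals and p-values for change within each arm. Chance movement in a few schools could be reported as a significant rise in the FEAST arm, or as a significant shift among controls, next to the between-arm result of a non-randomized trial.

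**Working it through.** **1. What the model does to a pre-post difference.** Write the outcome of pupil i in school j at time t as mean + β·t + u_j + b_ij + e_ijt. The T2 minus T1 difference is β + (e_ij2 − e_ij1), so u_j and b_ij cancel. If schools really change by different amounts, the difference also contains v_j2 − v_j1, which all pupils in the school share. The model has no term for this and puts it in the residual as if it were independent between pupils.

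This was checked by fitting the model (school and pupil intercepts, fixed time) to simulated data with 10 schools of unequal size. The standard error of time was compared with that of the paired t-test on all pupils:

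| School-level T1–T2 correlation in the data | Mixed-model SE | Paired t-test SE |
|---|---|---|
| 1.0 | 0.067405 | 0.067405 |
| 0.5 | 0.063621 | 0.063621 |

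**2. Inputs.** From Sample size: 10 schools per arm; CV 0.436; ICC 0.04; pre-post correlation r = 0.5; SD 1.3 (vegetables) and 1.1 (fruit); 20% loss, so 50 becomes 40 pupils. The text reads "with an average of 50 students (SD ± 22, and therefore CV = 0.436) per arm", but the stated power is reached only if 50 is the size of a school. Taken literally as 50 per arm, power would be about 35% (vegetables) and 48% (fruit). The school-level correlation over time, called CAC below, is not in the article and is an assumption.

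**3. The plan's own figure.** Between-arm power, with variance SD²(1 − 0.5²), design effect 1 + ((1 + CV²)m − 1) × 0.04, alpha 0.025 two-sided, an effect of 0.5 serves and a t distribution with 18 df:

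- Design effect: 2.864 at m = 40 and 3.340 at m = 50.
- Vegetables: 88.6% at m = 40 and about 91% at m = 50, against the stated 90%.
- Fruit: 96.6% and 97.6%, against the stated 97%.

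The inputs therefore reproduce the stated power.

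**4. Error rate of the within-group test when mean change is zero.**

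- Variance of a pupil's change: 2(1 − r)SD². For vegetables this is 2 × 0.5 × 1.69 = 1.69.
- School part of that variance: 2 × 0.04 × SD² × (1 − CAC).
- ICC of change: 2 × 0.04 × (1 − CAC) / (2 × 0.5) = 0.08 × (1 − CAC).
- Design effect of change: 1 + (1.190 × 40 − 1) × ICC of change = 1 + 46.60 × ICC of change.
- Rejection rate at nominal 5%: 2 × [1 − Φ(1.96/√design effect)].

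| CAC (assumed) | ICC of change | Design effect | Rejection rate | Simulated (6,000 runs) | SD of true change between schools, vegetables |
|---|---|---|---|---|---|
| 1.0 | 0 | 1.00 | 5.0% | 5.0% | 0 |
| 0.9 | 0.008 | 1.37 | 9.4% | 10.0% | 0.12 |
| 0.8 | 0.016 | 1.75 | 13.8% | 13.1% | 0.16 |
| 0.7 | 0.024 | 2.12 | 17.8% | 17.4% | 0.20 |
| 0.5 | 0.040 | 2.86 | 24.7% | 25.5% | 0.26 |

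The SD cancels from the rejection rate, so fruit gives the same rates. The last column is √(2 × 0.04 × 1.69 × (1 − CAC)) in serves per day. All its values are small against the 0.5-serve target.

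**5. Interval width.** For vegetables the model's SE is √(1.69/400) = 0.065. At CAC 0.8 the correct SE is 0.065 × √1.75 = 0.086. At CAC 0.5 it is 0.065 × √2.86 = 0.110, so the reported interval has about 59% of the width it should have (1/√2.86).

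**6. With the school variation allowed for.** A test on school-mean changes with 9 df rejected 4.4% to 5.5% of the time in every simulated scenario.

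**The case against.** **The wording leaves room.** The within-group sentence speaks of random effects, not random intercepts, so a random time slope for school is not expressly excluded. The article is also a condensed account. This stands in part: if a school slope is intended, the text only needs to say so. It is not the natural reading, though, because time is listed only as fixed and the sentence is presented as parallel to a model with random intercepts. The point concerns a model the article states, not detail it omits.

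**The inflation is not in the document.** A reader might infer that the test rejects about a quarter of the time. That needs a CAC of 0.5, which the article nowhere states. If school effects are fully stable, the rate is 5%.

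**The sample size does not settle it.** A reader might infer that the plan itself assumes unequal drift, since the stated power is reproduced with ICC 0.04 on the baseline-adjusted variance. With a baseline slope of 0.5, the adjusted ICC is 0.04 × (1.25 − CAC)/0.75, which equals 0.04 only at CAC 0.5. But a planner who simply multiplied the two factors, without considering how adjustment alters the ICC, would get the same power. At a higher CAC the calculation would merely be conservative: about 96% for vegetables at CAC 0.8. The power statement does not establish a CAC.

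**The consequence is limited.** Within-group changes are secondary to the intervention effect and no decision rule hangs on them. This stands, and it limits the weight of the point. They will still be reported with intervals and p-values, which should be valid.

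**Conclusion.** The point holds for the within-group changes. On its natural reading, the stated model ignores differences between schools in true change, so its 95% intervals are too narrow and its p-values too small whenever such differences exist. The article's own account of training, funding and delivery makes them likely.

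Under the assumptions in the working, the nominal 5% test rejects between about 5% (CAC 1.0) and 25% (CAC 0.5) of the time, with 9% to 14% at CAC 0.9 to 0.8. The range should be quoted, not one value.

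Two further inferences are not supported. A reader might say that the model tests a different hypothesis, namely that no school drifts. It does not: the time coefficient still targets mean change, and only its standard error is at fault. A reader might also carry the fault over to the primary comparison. That model has one follow-up outcome per pupil, a baseline covariate and a school intercept, so school variation enters its school effect.

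The figures apply to continuous outcomes with complete pairs. No rates were computed for binary outcomes or for multiply imputed data, where they would differ. The change is worth making before analysis, but it does not threaten the main result.

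**What to change.** In Statistical analysis, specify the within-group model with a random school-by-time effect in addition to the school and individual intercepts, and with small-sample degrees of freedom (about 10 − 1 = 9 per arm). Name an analysis of school-level changes as the fallback if the model does not converge. Use the same model for the pre-post mean-difference intervals under Primary outcomes.

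This takes about a sentence of text and one variance term, with no new data. The price is wider within-group intervals. For vegetables the half-width is now about 1.96 × 0.065 = 0.13 serves per day. With 9 df (t = 2.262) it would be roughly 2.262 × 0.086 = 0.19 at CAC 0.8 and 2.262 × 0.110 = 0.25 at CAC 0.5. Some binary outcomes may not support the extra term, hence the fallback.

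### The 0.025 threshold for the two primary outcomes is not carried into the analysis section, which reports 95% intervals; Holm with 95% intervals labelled unadjusted would settle this and add power

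*Protocol article*

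**What the plan says.** The Primary outcomes section of the protocol article defines two of them: "There will be two primary outcome measures: individual fruit (excluding juices) and vegetable (including potatoes and legumes) consumption", in serves per day. The Sample size section draws the consequence for testing, "a Bonferroni-corrected alpha (α) of 0.025 (i.e. 0.05/2) will be used", and the stated power of 90% (vegetables) and 97% (fruit) rests on that level.

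The Statistical analysis section describes the mixed models and then sets one reporting format for all of them. Intervention effects and within-group changes "will be reported as unstandardized regression coefficients or exponentiated coefficients (e.g. odds ratios), with 95% confidence intervals" and p-values. It makes no exception for the two primary outcomes and does not repeat the 0.025 level. The article does not say how a 95% interval is to be read against that level.

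The Primary outcomes section also mentions 95% intervals, but attaches them to the change from baseline to post-intervention rather than to a between-arm effect. It therefore supports the point only weakly.

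**The concern.** A two-sided test at 0.025 corresponds to a 97.5% interval, and a 95% interval corresponds to a test at 0.05. Where the p-value falls between the two levels, the reported interval and the stated criterion point in opposite directions. The article does not say which one governs.

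The trial accepted the stricter level when it was sized. A reader who sees only the analysis section could judge fruit and vegetables by their 95% intervals and lose that protection. The design is also non-randomised, and the Discussion presents the pre-specified analysis plan as a safeguard against bias. That safeguard is stronger if the success criterion stands in the analysis section.

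**Working it through.** **Inputs (Sample size section).** 10 schools per arm; mean 50 students, CV 0.436; 20% loss, so 50 × 0.8 = 40 analysed; ICC 0.04; baseline to follow-up correlation 0.5; SD 1.3 (vegetables) and 1.1 (fruit); effect 0.5 serves/day; alpha 0.025 per outcome.

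**Assumptions added here.** The test is two-sided. Baseline adjustment multiplies the variance by 1 − 0.5² = 0.75. The reference distribution is t with 20 − 2 = 18 df. The figure of 50 is taken per school. The text says "with an average of 50 students (SD ± 22, and therefore CV = 0.436) per arm", but 50 per arm would be 5 per school and give only 36-42% power for vegetables and 50-56% for fruit, so that reading cannot underlie the stated power.

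**Step 1: the plan's own power.**
- Design effect = 1 + ((1 + 0.436²) × 40 − 1) × 0.04 = 2.864.
- SE = SD × √(2 × 0.75 × 2.864 / 400), which is 0.1347 for vegetables and 0.1140 for fruit.
- Noncentral t power at 0.025 is 88.6% and 96.6%. With 50 analysed per school it is 90.8% and 97.6%. The stated 90% and 97% are reproduced to within two points.
- At alpha 0.05 with 40 per school, power is 93.9% and 98.5%. The vegetable figure then no longer matches, so the plan did use 0.025.

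**Step 2: where interval and criterion disagree.**
- Multipliers for 95% and 97.5% intervals are 1.960 and 2.241 (normal; ratio 1.144), or 2.101 and 2.445 (t, 18 df; ratio 1.164).
- Multiplying the t values by the SEs gives the estimates affected: 0.283 to 0.329 serves/day for vegetables and 0.240 to 0.279 for fruit.
- Example, vegetables with t = 2.25: estimate 2.25 × 0.1347 = 0.303, p = 0.037, 95% interval 0.020 to 0.586, 97.5% interval −0.026 to 0.633.

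**Step 3: how often.** This is P(2.101 < |T| < 2.445), with T noncentral t on 18 df and noncentrality equal to effect/SE.

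| True effect (serves/day) | Vegetables | Fruit |
|---|---|---|
| 0 | 2.5% | 2.5% |
| 0.25 | 11.6% | 12.6% |
| 0.30 | 12.6% | 12.0% |
| 0.50 | 5.3% | 1.9% |

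**Step 4: what Holm changes.** Holm compares the smaller p-value with 0.025 and, if that passes, the larger with 0.05.
- With no effect on either outcome, an error still needs the smaller p-value to reach 0.025. The family-wise error is therefore Bonferroni's: 1 − 0.975² = 4.94% if the outcomes are independent. If only one outcome has a true effect, the other is tested at 0.05 at most, so the 5% bound holds.
- Simulated power at 0.5 serves for both outcomes (t, 18 df, correlation 0 to 0.4) rises from 0.886 to 0.935-0.938 for vegetables and from 0.966 to 0.980-0.983 for fruit.

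**Step 5: which interval goes with which test.**
- Holm with 97.5% intervals: the second outcome can be declared significant at p between 0.025 and 0.05 while its 97.5% interval includes the null value. The frequency is Holm power minus Bonferroni power. For vegetables at the design effect this is 0.935 to 0.938 less 0.886, about 5%, close to the present 5.3%.
- Holm with 95% intervals: disagreement remains only when neither p-value reaches 0.025. At the design effect it is 0.939 less 0.935 to 0.938 (0.1 to 0.4 points) for vegetables and 0.985 less 0.980 to 0.983 (0.2 to 0.5 points) for fruit. With no effect and independent outcomes it is 0.025 × 0.975 = 2.4% per outcome, so the intervals still need the unadjusted label.

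**The case against.** The strongest reply is that there is no formal contradiction. A 95% interval is valid for estimation, a corrected alpha is for testing, and a plan may use both. P-values are reported beside the intervals, and a reader who knows the Sample size section can compare them with 0.025. The sentence on 95% intervals is a general format for all models, not a decision rule. A journal article may also leave this pairing to an analysis plan that is not shown. All of this stands and limits the point to a minor one. What remains is that the article itself fixes both levels and does not connect them.

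Three stronger readings are tempting and are not supported.
- A reader might infer that the trial will run its primary tests with a family-wise error of 1 − 0.95² = 9.75%. That figure assumes independent outcomes and arises only if the intervals are used as tests and the stated 0.025 is ignored.
- A reader might infer that the plan promised 95% joint coverage and fails to deliver it. The article sets a test level and makes no promise about joint coverage.
- A reader might infer that Bonferroni is an error. It is valid and controls the family-wise error; Holm is an improvement, not a correction.

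**Conclusion.** The point holds as a minor inconsistency of reporting and decision rule, confined to the two primary between-arm effects. No correction is stated for the secondary outcomes, so no conflict arises there. For 0.025 < p < 0.05 the reported interval excludes the null value (zero for a difference, one for a ratio) while the stated criterion is missed. Per outcome this happens about 2.5% of the time with no effect, 12-13% at 0.3 serves/day, and 5% (vegetables) or 2% (fruit) at 0.5.

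The sample size, the estimates and the p-values are unaffected. The substantive gain on offer is Holm's power: about 5 points for vegetables and 1 to 2 points for fruit, with no extra data. These sizes rest on two-sided tests, 40 analysed students per school, baseline adjustment with correlation 0.5, and t with 18 df. The Holm gains also assume an effect of 0.5 serves on both outcomes.

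**What to change.** Add to the Statistical analysis section, before the primary outcomes are analysed, that:
- the fruit and vegetable between-arm effects are tested by Holm at family-wise 0.05 (smaller p-value against 0.025, then the other against 0.05);
- their 95% intervals are unadjusted for multiplicity;
- the Holm decision, not the interval, determines significance.

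If plain Bonferroni is preferred, report 97.5% intervals for the two primary effects instead. These are 14% (normal) to 16% (t, 18 df) wider. Do not combine Holm with 97.5% intervals.

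The cost is two or three sentences. The sample size does not change, and under the Holm option neither do the intervals.

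### For the primary outcomes, the complete-case sensitivity analysis rests on nearly the same missing-data assumption as the multiple imputation, so it largely misses its stated purpose

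*Protocol article*

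**What the plan says.** All of this is in the protocol article, mainly under Statistical analysis.

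- Main approach: "missing data will be handled using multiple imputation by chained equations".
- Content of the imputation: "Imputation of outcome variables (and covariates if missing) will be conducted separately by intervention group and will include schools and covariates as auxiliary variables".
- Intervention-effect models: generalised linear mixed models with a random intercept for school and a fixed effect of arm. "Models will be adjusted for potential confounders: gender, grade, ICSEA, type of teacher training" and language spoken at home. In addition, "Analyses will also adjust for baseline levels of the desired outcome".
- Within-group change models: random effects for schools and individuals and a fixed effect of time. No baseline covariate is mentioned.
- Aim of the missing-data check: "To assess sensitivity of the findings to different assumptions around the missing data mechanism".
- The one analysis named for that aim: "complete case analyses (valid under a missing completely at random assumption) will also be conducted as a sensitivity analysis".
- Expected loss, under Sample size: "Allowance will be made for 20% loss due to follow-up or missing data".

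The Discussion lists missing-data methods and sensitivity analyses among the safeguards against bias in a non-randomised design, and says the article includes them.

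**The concern.** A sensitivity analysis for missing data is informative when it changes the assumption about why data are missing. The article presents complete case as doing so, with MCAR on one side and the imputation's missing-at-random condition on the other.

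For the effect models that contrast is mostly nominal. When only the T2 outcome is missing, regression on the observed pupils is consistent if missingness depends on arm, baseline outcome, the listed covariates and school, because all of these are conditioned on. MCAR is sufficient but not necessary. The imputation names essentially the same variables. Neither analysis allows missingness to depend on the T2 intake that was not observed.

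At stake is the reading of the result. The trial is unblinded and relies on children's self-report, with 20% loss allowed for. If dropout were related to T2 intake, the two analyses would be wrong by about the same amount, and their agreement would give no warning.

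**Working it through.** **Inputs (Sample size).** 10 schools per arm; mean 50 pupils, CV 0.436; ICC 0.04; baseline-to-follow-up correlation 0.5; SD 1.3 (vegetables) and 1.1 (fruit) serves/day; effect 0.5 serves/day; alpha 0.025, taken as two-sided; 20% loss. The 50 pupils are read as per school, because the stated power reproduces only on that reading.

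**1. Reproduce the plan's power.**
- Pupils per school after loss: 50 × 0.8 = 40.
- Design effect: 1 + [(0.436² + 1) × 40 − 1] × 0.04 = 2.864.
- Effective n per arm: 400 / 2.864 = 139.7.
- Residual SD: SD × √(1 − 0.5²), which is 1.126 (vegetables) and 0.953 (fruit).
- SE of the arm effect: residual SD × √(2 / 139.7), which is 0.135 and 0.114.
- Power from a noncentral t with 18 df: 88.6% and 96.6%, against 90% and 97% stated. This agrees within 2 points, so these SEs suit what follows.

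**2. Do the two analyses respond differently to the mechanism?** 1,500 simulated trials per mechanism used the vegetable inputs: 20 schools of 50, true effect 0.50, about 20% of T2 outcomes missing. Complete case was least squares on arm, baseline and one covariate, with no school random intercept. Imputation was by arm, using school, baseline and that covariate, with 10 imputations. Monte Carlo error is about 0.003.

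| Missingness depends on | Complete case | Imputation |
|---|---|---|
| Nothing (MCAR) | 0.503 | 0.503 |
| Baseline, arm, covariate (25% vs 15% missing) | 0.501 | 0.501 |
| T2 intake, both arms | 0.454 | 0.455 |
| T2 intake, intervention arm only | 0.664 | 0.661 |

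The second row is not MCAR, yet the adjusted complete-case estimate is unbiased; the unadjusted one is 0.599. In the last two rows both methods carry the same bias. Across trials the estimates correlate at 0.98 to 0.99 and differ by 0.01 to 0.02 on average.

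**3. Within-group change.** In the second scenario, the simple mean change among intervention pupils with both surveys was 0.317 against a true 0.50. For those models, if complete case means pupils with both surveys, the MCAR label is about right.

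**4. Illustrative size.** If the 20% of intervention pupils who are missing gained 0 instead of 0.5, and controls had no offsetting loss, the true effect is 0.8 × 0.5 + 0.2 × 0 = 0.40, while both analyses give about 0.50. The bias of 0.10 is 0.10 / 0.135 = 0.74 SE (vegetables) or 0.10 / 0.114 = 0.88 SE (fruit).

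**5. Tipping point.** Shift the imputed intervention-arm T2 values by delta: estimate = 0.50 + 0.20 × delta. Hold the SE at its step 1 value. The critical t (18 df, two-sided 0.025) is 2.445.
- delta −0.25, −0.5, −1.0 gives 0.45, 0.40, 0.30.
- Smallest significant effect: 2.445 × 0.1347 = 0.329 (vegetables); 2.445 × 0.114 = 0.279 (fruit).
- Tipping delta: (0.329 − 0.50) / 0.20 = −0.85; (0.279 − 0.50) / 0.20 = −1.11.
- For an observed vegetable effect of 0.40: (0.329 − 0.40) / 0.20 = about −0.35.

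**The case against.** Five points can fairly be made for the plan.

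- **The parenthesis is not false.** It says complete case is valid under MCAR, not only under MCAR, and it covers all the models, including the within-group ones. This stands: the label is imprecise for the effect models and should stay for the change models.
- **The two analyses are not identical.** A reader might infer that they share exactly one assumption and must agree. The documents do not support that. The imputation "will be conducted separately by intervention group and will include schools and covariates as auxiliary variables", which is not an exclusive list. Several outcomes are imputed by chained equations and might inform one another. Missing covariates are provided for, and the baseline outcome comes from a separate survey. In each case the assumptions can diverge more, and the simulation, which used the narrow imputation model with only T2 missing, does not speak to them.
- **An unseen analysis plan might add more.** It might, and a missing detail would not be a finding. The point here is that the article states an aim and assigns to it an analysis that mostly cannot serve it.
- **Dropout may not be informative.** Surveys are done at a class time set by the teacher in both arms, with reminders and a school voucher for completion. Nothing in the article shows that disengaged intervention pupils are the likeliest to be missing. This stands: the 0.10 is an illustration.
- **A target-sized result would survive it.** At delta −0.5 the estimate of 0.40 gives t of about 3.0 (vegetables) and 3.5 (fruit) against 2.445. This stands, and is why the range of deltas must go further.

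**Conclusion.** The point holds for the intervention-effect models and missing T2 outcomes. There, complete case and the described imputation rest on nearly the same missing-at-random condition, and in simulation they shared the same bias when loss depended on T2 intake (0.454 and 0.455, or 0.664 and 0.661, against 0.50). The aim of testing different missing-data assumptions is therefore largely unmet.

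This rests on the imputation using about the variables named and on baseline and covariates being mostly complete. The 0.10 serves/day, a fifth of the target effect, also assumes that the 20% of intervention pupils who are missing gained nothing and that controls had no offsetting loss.

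A reader might go on to infer that the primary analysis is invalid or that dropout will bias it. The documents support neither. The main analysis stands; what fails is most of the reassurance that agreement with complete case could offer.

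**What to change.** 1. For the intervention-effect models only, replace the MCAR parenthesis with wording such as: *valid when missingness depends only on variables in the model*. Keep the MCAR label for the within-group change models.
2. Prespecify a delta-adjusted (pattern-mixture) analysis by arm for both primary outcomes, run on the existing imputations. Extend delta until the conclusion changes and report that tipping point. At an observed effect of 0.5 with 20% missing, the range must reach about −0.85 serves/day for vegetables and −1.1 for fruit; a range ending at −0.5 would stop short. The article gives no delta values, so the range needs its own justification.

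Complete case can stay as a secondary check. The cost is a few lines of code and one more results table, with no new data.
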